## Abstract

**Background:**

Low-level laser therapy (LLLT) has been shown to modulate the inflammatory process without adverse effects , by reducing pain and swelling and promoting the repair of damaged tissues. Because pain, swelling and muscle spasm are complications found in virtually all patients following oral surgery for the removal of impacted teeth, this model has been widely used to evaluate the effects of LLLT on the inflammatory process involving bone and, connective tissue and the muscles involved in mastication.

**Methods/Design:**

After meeting the eligibility criteria, 60 patients treated at a Specialty Dental Center for the removal of impacted lower third molars will be randomly divided into five groups according to the type of laser therapy used at the end of surgery (intraoral irradiation with 660 nm laser; extraoral irradiation with 660 nm laser; intraoral irradiation with 808 nm laser; extraoral irradiation with 808 nm laser and no irradiation). To ensure that patients are blinded to the type of treatment they are receiving, the hand piece of the laser apparatus will be applied both intraorally and extraorally to all participants, but the device will be turned on only at the appropriate time, as determined by the randomization process. At 2 and 7 days after surgery, the patients will be evaluated by three blinded evaluators who will measure of swelling, mouth opening (muscle spasm evaluation) and pain (using two different pain scales). The 14-item Oral Health Impact Profile (OHIP-14) will be used to assess QOL. All data will be analyzed with respect to the normality of distribution using the Shapiro-Wilk test. Statistically significant differences between the experimental groups will be determined using analysis of variance, followed by a suitable *post hoc* test, when necessary. The significance level will be set at α = 0.05.

**Discussion:**

The lack of standardization in studies with regard to the samples, methods and LLLT parameters complicates the determination of the actual effect of laser therapy on this model. The present study aims to provide a randomized, controlled, double-blind trial to compare four different LLLT parameters in relation to the outcomes of pain, swelling and muscle spasm following surgery for the extraction of impacted third molars and evaluate the effects os surgery on patients' quality os life (QOL).

**Trial registration:**

Brazilian Registry of Clinical Trials - Rebec (RBR-6XSB5H).

## Background

Low-level laser therapy (LLLT) has been shown to modulate the inflammatory process without adverse effects, by reducing pain and swelling and promoting the repair of damaged tissues [1,2]. The effect of LLLT on acute pain from a soft-tissue injury may be related to the consequent reduction in edema, hemorrhage, neutrophil infiltration, inflammatory cytokines and enzymes [3]. The swelling-reduction effect of LLLT may be related to its ability to accelerate the regeneration of lymph vessels and decrease vascular permeability [4-6].

A large number of reports exist regarding the effect of LLLT on the tissue repair process, especially the inflammatory processes that affect muscle tissue [7-10]. However, studies addressing the effects of LLLT on muscle spasms caused by the inflammatory process have reported conflicting results [11-17].

Because the removal of impacted third molars involves damage to bone, and connective tissue and the muscles involved in mastication, this model has been widely used to evaluate the effect of LLLT on the inflammatory process [1,18,19]. Indeed, a considerable number of studies have evaluated the effect of LLLT on reductions in pain, swelling and muscle spasm following the surgical removal of impacted third molars, but the lack of standardization in the methods and dosimetric parameters used has compromised evaluation of the desired outcomes and hinders the acceptance of LLLT as an effective method for minimizing the adverse effects of third molar surgery [1].

In the literature, eight articles have assessed pain [11,12,15-17,20-22]. Only studies that used intraoral application of red laser irradiation reported a reduction in postoperative pain, but the parameters were not fully described in any of these articles [20,21].

With regard to swelling [11-17,22,23], a reduction in postoperative edema was obtained in one study that used red laser (50 mW, 4 J/cm^2^) applied intraorally [23], one that used infrared laser (100 mW, 12 J, 4 J/cm^2^) extraorally [14] and two that used infrared laser (100 mW, 12 J, 4 J/cm^2^ and 300 mW, 54 J, respectively) with a combination of intraoral and extraoral irradiation [13,17].

Concerning muscle spasm [11-17], a reduction was found in one study that used red laser (300 mW, 10 J/cm^2^) intraorally [16], two studies that used infrared laser (100 mW, 120 12 J, 4 J/cm^2^ and 300 mW, 54 J) both intraorally and extraorally [13,17], and one study that used infrared laser (100 mW, 12 J, 4 J/cm^2^) either extraorally or intraorally [14].

The aim of the proposed project is to carry out a randomized, controlled, double-blind, clinical trial evaluating the effects of LLLT on pain, swelling and muscle spasm following surgical removal of impacted third molars. Comparisons will be made of two sites (intraoral versus extraoral) and different laser wavelengths (red versus infrared).

## Methods/Design

### Study location

This randomized, controlled, double-blind, clinical trial will be carried out in the Specialty Dental Center of the city of São Bernardo do Campo, state of São Paulo, Brazil.

### Study design and composition of study sample

The study design will consist of five treatments evaluated on two occasions (at 2 and 7 days following surgery). Table 1 shows the scheme for repeated-measures analysis of variance. Because the measures of pain, swelling and mouth opening have low variability when using the proposed scales, 40 degrees of freedom will be sufficient to control for residual variance. Thus, a minimum sample size of 50 subjects (10 in each group) is sufficient. Thus 50 patients undergoing treatment at the center for the removal of impacted lower third molars will participate in the study.

**Table 1 T1:** Scheme for repeated-measures analysis of variance

**Causes of variation**	**Degrees of freedom**
Treatment	4
Period	1
Treatment × period	4
Residual	40
Total	49

In addition, as this work predicts a two-factor (two wavelength), two-group (two irradiation sites) analysis, there will be 20 patients in each group (10 in each experimental subgroup) and 20 in control group. The power analysis (Figure 1) shows that for medium and large effect size, the test power will remain above 0.8 for 20 subjects in each group.

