##### Evaluation of postoperative swelling

Postoperative swelling reaches a peak 12 to 48 h following third molar extraction and begins to decrease during the subsequent days, disappearing around 5 to 7 days postoperatively [19,23,26,27]. To measure swelling, most authors measure the distance between two [11,13,14,23] or three predetermined anatomical points on the face [15]. In the present study, the same three evaluators mentioned above will measure the distances between the corner of the eye and angle of the mandible, between the tragus and lip commissure and between the tragus and pogonion of each patient 2 and 7 days following surgery.

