### Statistical analysis

All data will be analyzed with respect to the normality of distribution using the Shapiro-Wilk test. Statistically significant differences between the experimental groups will be determined using analysis of variance, followed by a suitable post hoc test, if necessary. The significance level will be set at α = 0.05. By assuming normality in the distribution of the data, two-way ANOVA offers a high power for the design of this trial.

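### The repeated-measures ANOVA named for days 2 and 7 would, in its classical form, lose a patient's day 2 value if day 7 is missed; a mixed model on all available visits avoids this

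*Protocol article*

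**What the plan says.** All places are in the protocol article.

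- **Study design and composition of study sample**, on the visits: "The study design will consist of five treatments evaluated on two occasions (at 2 and 7 days following surgery". On the analysis: "Table 1 shows the scheme for repeated-measures analysis of variance". Table 1 lists treatment (4 degrees of freedom), period (1), treatment × period (4) and one residual (40), total 49. It has no line for patients.
- **Same section**, on size: "40 degrees of freedom will be sufficient to control for residual variance", and then "Thus, a minimum sample size of 50 subjects (10 in each group) is sufficient".
- **Randomization and composition of groups** allocates 10 patients to each of four laser arms and 20 to control, which makes 60.
- **Statistical analysis** names analysis of variance with a post hoc test and adds that "two-way ANOVA offers a high power for the design of this trial". It does not call this analysis repeated-measures.
- **Evaluation of results** makes pain, swelling and muscle spasm primary at both visits and ranks neither day first.
- **Evaluation of postoperative swelling** says that swelling "begins to decrease during the subsequent days, disappearing around 5 to 7 days postoperatively". For pain, the article describes a gradual decline up to day 7. For mouth opening it gives no time course.

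**The concern.** Two models can be read from the article, and each has a weakness.

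A classical repeated-measures ANOVA works on complete patients. A patient seen on day 2 but not on day 7 then leaves the analysis of both days. The laser arms hold exactly the 10 patients that the article calls the minimum, so there is no reserve. If attendance at day 7 depends on how well the patient has recovered, the patients left on day 2 are also a selected group.

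A two-way ANOVA over treatment and period without a patient term keeps every row but ignores that two rows come from the same patient. Its treatment test then rests on the wrong error term.

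At stake are the precision of the day 2 results, the validity of the standard errors and, less certainly, some bias.

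**Working it through.** **1. Table 1 against the named method.** For 50 patients at 2 visits, a repeated-measures layout has 50 × 2 − 1 = 99 total degrees of freedom: treatment 4 + patients within treatment 45 + period 1 + treatment × period 4 + within-patient residual 45. This is not 40 of 49. A two-way layout of 50 single values has 50 − 10 cells = 40 residual and 49 total, which matches Table 1 exactly. The printed scheme therefore does not settle which model will be run.

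**2. What each model does with a missed day 7.** On simulated data with 60 patients (10/10/10/10/20) and 6 day 7 values missing, 120 − 6 = 114 rows remain.
- A classical repeated-measures routine rejected the data as unbalanced. Complete-case use leaves 54 patients and discards 6 valid day 2 values.
- A two-way ANOVA without a patient term used all 114 rows (residual 114 − 10 = 104).
- A linear mixed model was fitted to the same 114 rows.

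**3. Cost of ignoring the pairing.** Let r be the day 2/day 7 correlation (assumed 0.3 to 0.7). The variance of a patient's two-visit mean is σ²(1 + r)/2, but the model without a patient term takes σ²/2. The variance for the treatment comparison is understated by a factor 1 + r = 1.3 to 1.7, so its test statistic is inflated by √1.3 = 1.14 to √1.7 = 1.30. For treatment × period the true factor is 1 − r = 0.7 to 0.3, so that test is too conservative.

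**4. Loss of precision under complete-case use.** No dropout rate is stated, so 5% to 20% is assumed. Power is for the five-group F test at day 2, α = 0.05 (from the article), assumed f = 0.40, noncentrality f² × n, degrees of freedom 4 and n − 5.

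| Missing day 7 | Completers | Day 2 values lost | Power, completers | Power, all 60 |
|---|---|---|---|---|
| 0% | 60 | 0 | 0.653 | 0.653 |
| 5% | 57 | 3 | 0.625 | 0.653 |
| 10% | 54 | 6 | 0.595 | 0.653 |
| 15% | 51 | 9 | 0.565 | 0.653 |
| 20% | 48 | 12 | 0.532 | 0.653 |

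At 5% independent absence, the chance that at least one of the 40 laser patients misses day 7, and so takes an arm below 10 completers, is 1 − 0.95⁴⁰ = 0.87.

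**5. Possible bias.** Assumed: day 2 VAS mean 5 in control and 4 under laser, SD 2, clipped to 0–10; 25% to 40% of patients with VAS below 3 miss day 7, against 5% of the others. The share below 3 is Φ(−1) = 0.159 in control and Φ(−0.5) = 0.309 under laser.
- At 25%, deleted: control 0.159 × 0.25 + 0.841 × 0.05 = 8.2%; laser 0.309 × 0.25 + 0.691 × 0.05 = 11.2%.
- At 40%, deleted: control 0.159 × 0.40 + 0.841 × 0.05 = 10.6%; laser 0.309 × 0.40 + 0.691 × 0.05 = 15.8%.
- The day 2 difference is 0.98 in all patients, 0.93 in completers at 25% and 0.88 at 40%, a loss of 5% to 10%.
- The standard error of a 10 versus 20 comparison is 2 × √(1/10 + 1/20) = 0.77. A bias of 0.05 to 0.10 is 0.06 to 0.13 of it.
- If absence is unrelated to the outcome, there is no bias.

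**The case against.** The strongest reply is that this is a missing-data question, which a condensed article may leave to a full protocol or analysis plan. That stands as far as silence goes: the lack of a dropout rate or a missed-visit rule is not counted here. The point is about a method that the article does name.

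Three stronger readings are tempting, and the article supports none of them.

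- *The protocol deletes patients who miss day 7.* It nowhere says so. Deletion follows from the classical form of the named method. Table 1 and the Statistical analysis section can be read as a model that keeps the day 2 value, though at the price shown in step 3.
- *The protocol expects all symptoms to have gone by day 7.* It says this of swelling only. The pain text describes a decline, and the mouth-opening text is silent.
- *The bias is certainly towards no effect.* That needs well-recovered patients to stay away more often, which the article does not say. Follow-up lasts only a week and OHIP-14 is collected at day 7, so attendance may be good. A different pattern of absence would act differently.

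It is also fair that no day 2 contrast is given priority, and that the illustrated bias is small beside the sampling error.

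**Conclusion.** The point holds in conditional form and is minor. As named, the analysis either discards valid day 2 values when day 7 is missed (classical repeated-measures ANOVA) or ignores the pairing of visits (two-way ANOVA without a patient term).

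Under the first reading, the surer cost is precision: about 0.03 to 0.12 of day 2 power at 5% to 20% absence, given f = 0.40. Bias is only possible. Under the selective absence assumed above it is 0.05 to 0.10 VAS points. Attendance rates, effect sizes and the correlation are all assumptions, because the article gives none. With full attendance the first cost is zero. The second does not depend on attendance.

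**What to change.** In both the study design section and the Statistical analysis section, name one model for each continuous primary outcome: a likelihood-based linear mixed model with treatment, visit and treatment × visit, an unstructured within-patient covariance over the two visits, and small-sample degrees of freedom. Fit it to all available visits of all randomised patients in their allocated arm. Report the treatment effects at day 2 and at day 7. Replace Table 1 to match.

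This needs no extra patient or visit, and with complete data it agrees closely with a correctly specified repeated-measures ANOVA. Its downside is an assumption that missing day 7 values are explained by arm and the day 2 value. That is weaker than what deletion requires, but it cannot be verified from the data.

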### Randomization and composition of groups

After undergoing a clinical evaluation by the dental surgeons, patients who meet the eligibility criteria will be divided into five experimental groups (Figure 2) based on a randomization method involving raffle numbers. Randomization will be conducted by a researcher not involved in the recruitment and treatment of the participants. Concealed allocation will be performed using a set of random numbers placed in sealed opaque envelopes. The laser operator will open the envelope containing the procedure to be performed on each patient immediately following third molar surgery. Sealed envelopes awaiting new subjects will be kept in a safe place and given to the operator as the sessions are scheduled. The 40 patients will be allocated into four experimental groups or a control group as follows: Group 1 (660 nm laser, applied intraorally, n = 10), Group 2 (808 nm laser, applied intraorally, n = 10), Group 3 (660 nm laser, applied extraorally, n = 10), Group 4 (808 nm laser, applied extraorally, n = 10), Group 5 (control; no irradiation, n = 20).

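### Table 1 is labelled a repeated-measures ANOVA but has no patient term and counts 50 observations where the design yields 100 to 120, so the 40-degrees-of-freedom case for 50 patients is wrong

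*Protocol article*

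**What the plan says.** Under Study design and composition of study sample, the protocol article describes "five treatments evaluated on two occasions (at 2 and 7 days following surgery"), and adds that "Table 1 shows the scheme for repeated-measures analysis of variance". The table lists treatment 4, period 1, treatment × period 4, residual 40 and total 49. There is no row for patients.

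The text then claims that "40 degrees of freedom will be sufficient to control for residual variance" and concludes that "a minimum sample size of 50 subjects (10 in each group) is sufficient". The same section goes on to a two-wavelength by two-site analysis with 20 patients per group and a power figure that is not reproduced.

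The Abstract gives a different total: "60 patients treated at a Specialty Dental Center for the removal of impacted lower third molars will be randomly divided into five groups". Randomization and composition of groups lists four laser groups of 10 and "Group 5 (control; no irradiation, n = 20"), which also makes 60.

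Statistical analysis names analysis of variance and says "By assuming normality in the distribution of the data, two-way ANOVA offers a high power for the design of this trial". It does not say which two factors are meant, and it mentions no patient effect. Evaluation of results confirms that the three primary outcomes (pain, swelling, muscle spasm) are assessed at both visits.

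**The concern.** In a repeated-measures design with patients nested in treatment there are two error terms. Treatment is compared with the variation between patients. Period and treatment × period are compared with the variation within patients. A table for such a design must therefore contain a patients-within-treatment row. Table 1 has a single residual for everything, which is the layout of an ordinary 5 × 2 ANOVA on unrelated observations.

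Two things follow. First, the residual of 40 df is the stated reason for a minimum of 50 patients, and that figure does not belong to this design. Second, anyone who followed the table literally with both visits in the data would test treatment against the wrong error term on the three primary outcomes, and would test the difference in time course against an error term that is too large.

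**Working it through.** **Inputs.** Five treatments and two visits per patient (Study design and composition of study sample). Fifty patients, 10 per group (same section), or 60 as 4 × 10 + 20 (Abstract; Randomization and composition of groups). α = 0.05 (Statistical analysis). The documents do not give the correlation ρ between a patient's day-2 and day-7 values, so it is an assumption and a range is shown.

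**1. The plan's own figure.** 49 − 4 − 1 − 4 = 40. The subtraction is right, but a total of 49 means 50 observations, or five in each of the 5 × 2 cells.

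**2. What the design yields.**
- 50 patients × 2 visits = 100 observations, total 99 df.
- 60 patients × 2 visits = 120 observations, total 119 df.
- 25 patients × 2 visits would give a total of 49, but the 40 would then split into 20 between and 20 within patients, and 25 patients contradicts 10 per group.

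None of these gives a single residual of 40 in a repeated-measures table.

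**3. The correct split.** Patients within treatment = N − 5; within-patient residual = (N − 5)(2 − 1) = N − 5.

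| Source | N = 50 | N = 60 |
|---|---|---|
| Treatment | 4 | 4 |
| Patients within treatment (error for treatment) | 45 | 55 |
| Period | 1 | 1 |
| Treatment × period | 4 | 4 |
| Within-patient residual | 45 | 55 |
| Total | 99 | 119 |

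**4. Consequence if both visits share one residual.** With variance σ² at both visits and no treatment effect, the expected treatment mean square is σ²(1 + ρ) and the expected treatment × period mean square is σ²(1 − ρ). The pooled residual, on 2(N − 5) df, has expectation σ²[(1 + ρ) + (1 − ρ)]/2 = σ². The treatment F ratio is thus too large by a factor of about 1 + ρ, and the interaction F ratio too small by a factor of about 1 − ρ.

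Simulated rejection rates at nominal 5% with no effect present (normal data, equal variances, 60 patients as 10/10/10/10/20, pooled residual 110 df):

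| ρ | Treatment, single residual | Treatment, between-patient error | Treatment × period, single residual |
|---|---|---|---|
| 0 | 5.1% | 5.0% | 5.0% |
| 0.3 | 11.8% | 5.1% | 1.0% |
| 0.5 | 17.3% | 5.0% | 0.1% |
| 0.7 | 22.7% | 5.0% | below 0.1% |

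With 50 patients (90 df) the single-residual treatment rates are 11.8%, 17.2% and 22.9% at ρ = 0.3, 0.5 and 0.7. With the critical value that Table 1 implies, F(4, 40), the 60-patient rates are 10.0%, 15.0% and 20.0%.

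**5. Unequal variances.** If the day-7 SD is r times the day-2 SD, the inflation factor becomes 1 + 2rρ/(1 + r²). For r = 1/2 this is 1 + 0.8ρ; for r = 1/3 it is 1 + 0.6ρ. Simulation with 60 patients gives about 11%, 14% and 19% for r = 1/2, and about 9%, 12% and 16% for r = 1/3, at ρ = 0.3, 0.5 and 0.7.

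**6. Power of the interaction test.** The rates in step 4 are null rejection rates, not power. For a treatment × period effect that the correct test would detect with power 0.80 (60 patients, equal variances), the single-residual test has power 0.61, 0.34 and 0.06 at ρ = 0.3, 0.5 and 0.7.

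**The case against.** The strongest reply is that the text names a repeated-measures method. Run as named, that method tests treatment against variation between patients, and Table 1 is only a planning scheme. A full analysis plan, not shown here, may include a patient term, and then no inflation occurs. This stands. A reader might infer from Table 1 that the trial's treatment test will use the wrong error term, or that its error rate will exceed 15%. The documents do not establish either. The first requires the table to be followed literally with both visits pooled. The second also needs, with equal variances, a correlation above 0.4 (14.5% at 0.4 and 15.9% at 0.45 with 60 patients), or of about 0.5 with the F(4, 40) critical value.

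Equal variances are also open to doubt. The article says that pain gradually falls until day 7 and that swelling disappears around days 5 to 7, so a smaller spread at day 7 is plausible for those outcomes. Step 5 shows that this weakens the inflation but does not remove it.

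A reader might also take the two-way ANOVA in Statistical analysis as a repeat of the treatment × period layout. That section does not name the factors. Wavelength × site is at least as natural a reading, since the Background gives those comparisons as the aim and the sample-size section describes that factorial. Analysed separately at each visit, it would raise no repeated-measures problem. The wording is ambiguous and does not corroborate the error in Table 1.

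Nor is the interaction test nearly powerless in general. That description fits only high correlations (power 0.06 at ρ = 0.7, but 0.61 at 0.3).

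Finally, the 40-df argument supports only a stated minimum, and a separate power analysis with 20 per group follows it. So the error does not by itself show that 60 patients are too few. What remains is that the table and the argument drawn from it are printed statements that do not fit the design, whatever a later plan contains.

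**Conclusion.** The point holds in this form. Table 1 is not the degrees-of-freedom table of the design it is said to describe: it lacks the patient term, and its total is 49 where 99 (50 patients) or 119 (60 patients) is required. The justification of 50 patients from 40 residual df is wrong as written. This follows from the document alone and needs no assumption.

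The effect on error rates is conditional. If both visits are analysed on a single residual, with 60 patients, normal data and equal variances, the nominal 5% treatment test rejects about 12%, 17% and 23% of the time at assumed correlations of 0.3, 0.5 and 0.7. The rates are lower if day-7 variance is smaller. Under the same condition the treatment × period test is conservative and loses power. Testing treatment against patients within treatment restores 5% throughout.

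**What to change.** 1. Replace Table 1 with treatment 4; patients within treatment 55, marked as the error term for treatment; period 1; treatment × period 4; within-patient residual 55; total 119. If the trial size is 50, the rows are 4, 45, 1, 4, 45 and the total 99.
2. Delete the argument from 40 degrees of freedom.
3. In Statistical analysis, state that any analysis using both visits includes a patient effect, either as a split-plot ANOVA or as a linear mixed model with treatment, day, treatment × day and a random patient effect.
4. In the same section, say which factors the two-way ANOVA refers to. Keep the wavelength and site comparison as contrasts among the four laser arms within that model. The 4 treatment df accommodate it: wavelength 1, site 1, wavelength × site 1, and laser versus control 1.

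The cost is one corrected table and a few sentences. No new data are needed, and the article reports that the trial was still collecting data at submission. The sample-size rationale would then rest on the separate power analysis.

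### The stated power above 0.8 for medium and large effects at 20 per group is not supported for treatment comparisons under conventional effect sizes

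*Protocol article*

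**What the plan says.** The section Study design and composition of study sample gives two justifications of size.

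- The first sets out a repeated-measures analysis of variance (Table 1: treatment, period, treatment × period, 40 residual degrees of freedom). It argues from those 40 degrees of freedom, and from the low variability of the scales, that "a minimum sample size of 50 subjects (10 in each group) is sufficient".
- The second concerns the wavelength and irradiation-site analysis. It says "there will be 20 patients in each group (10 in each experimental subgroup) and 20 in control group", and then that "for medium and large effect size, the test power will remain above 0.8 for 20 subjects in each group", with reference to Figure 1.

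The Statistical analysis section adds, assuming normality, that "two-way ANOVA offers a high power for the design of this trial". On alpha it says: "The significance level will be set at α = 0.05".

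The Randomization section gives four laser arms of 10 and a control arm of 20. The Background names the comparisons of interest: intraoral against extraoral, and red against infrared. The Evaluation of results section makes pain, swelling and muscle spasm the three primary outcomes. Swelling and mouth opening are compared with preoperative values; no preoperative pain measurement is described.

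**The concern.** The power sentence belongs to the wavelength and site grouping, so a reader will take it to cover comparisons between treatments. At 20 per group, a conventional medium effect is well short of 80% power for an ordinary between-group test. The degrees-of-freedom argument cannot fill the gap. Residual degrees of freedom determine how precisely the variance is estimated; they do not say which difference can be detected.

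What is at stake is the reading of a non-significant result. With a stated power above 0.8, it looks like fair evidence against a medium-sized benefit of a site or wavelength. With the power the design has for most such comparisons, it is weak evidence.

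**Working it through.** **Inputs from the article.** Alpha 0.05; groups of 20 (two pooled laser groups of 10 + 10, and control), total 60; two visits, days 2 and 7.

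**Assumptions.** Two-sided tests. Medium/large taken as f = 0.25/0.40 (three groups) or d = 0.5/0.8 (two groups). Between-visit correlation ρ from 0 to 0.9. No SD is needed for standardised effects.

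**The plan's own figure.** Above 0.8 for both sizes. It could not be reproduced for any comparison of treatment levels without baseline adjustment, as steps 1 to 3 show.

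**Step 1. One day, no baseline.**

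- Three groups of 20, noncentral F with 2 and 57 df, λ = f²N. Medium: 0.0625 × 60 = 3.75, power 0.374. Large: 0.16 × 60 = 9.6, power 0.776.
- 20 v 20, noncentral t with 38 df, δ = d/√(1/20 + 1/20). Medium: 0.5/0.316 = 1.58, power 0.338. Large: 0.8/0.316 = 2.53, power 0.693.
- Pooled laser v control (40 v 20): 0.435 / 0.819.
- Five arms of 10, the size the first justification calls sufficient: 0.231 / 0.554.
- One laser arm v control (10 v 20, error variance from all five arms, 60 − 5 = 55 df): 0.245 / 0.528.

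For 0.8 on one day, a medium effect needs about 53 per group (three groups) or 64 per group (two groups). A large effect needs 22 or 26.

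**Step 2. Mean of the two visits, 3 × 20, no baseline.** λ = f²N × 2/(1 + ρ).

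| ρ | 0 | 0.3 | 0.5 | 0.7 | 0.9 |
|---|---|---|---|---|---|
| Medium | 0.663 | 0.543 | 0.482 | 0.432 | 0.392 |
| Large | 0.976 | 0.928 | 0.887 | 0.843 | 0.798 |

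For a medium effect over ρ from 0 to 0.7, 20 v 20 gives 0.587 down to 0.387, and 40 v 20 gives 0.719 down to 0.495.

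**Step 3. More generous readings, medium effect.** One-sided test, 20 v 20, one day: 0.463. Treating all 120 observations as independent, which is wrong: 0.675. Neither reaches 0.8.

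**Step 4. Treatment-by-period interaction, 3 × 20.** λ = f²N × 2/(1 − ρ). Medium: 0.663 at ρ = 0, 0.822 at 0.3, 0.932 at 0.5. This test does pass 0.8 once ρ is about 0.3.

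**Step 5. Baseline adjustment (swelling and mouth opening only), medium effect in raw SD units.**

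- One day, pre-post correlation r, λ = f²N/(1 − r²). At r = 0.8: 3.75/0.36 = 10.4, power 0.81 for three groups (0.73 for 20 v 20). At r = 0.9, 20 v 20 gives 0.94.
- Mean of both visits, one correlation r throughout, λ = f²N/[(1 + r)/2 − r²], three groups: 0.66 at r = 0.5, 0.81 at 0.7 (3.75/0.36), 0.92 at 0.8. Change scores give 0.48, 0.71 and 0.88.

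**Step 6. Detectable difference at 80% power, one day, unadjusted.** With 55 df the noncentrality needed is about 2.852, so the detectable difference is 2.852 × √(1/n₁ + 1/n₂).

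- 40 v 20: 2.852 × 0.2739 = 0.78 SD.
- 20 v 20: 2.852 × 0.3162 = 0.90 SD.
- 10 v 20: 2.852 × 0.3873 = 1.10 SD.

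**The case against.** The strongest reply is that Figure 1 is not available and the text names neither test, effect size nor correlation. The design is framed as a repeated-measures analysis, and one of its listed tests, treatment by period, does exceed 0.8 for a medium effect at plausible correlations. A reader might infer that the authors simply miscalculated; that cannot be shown, since the figure may be correct for that test. What remains is that the sentence is attached to the wavelength and site grouping, while the interaction asks only whether the gap between groups changes from day 2 to day 7.

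A reader might also infer that a medium effect can never reach 0.8 in this trial. The article does not support that. Two of the three primary outcomes are compared with a preoperative value, and step 5 shows that a pre-post correlation of about 0.7 to 0.8 or more could carry a raw-SD medium effect past 0.8. The article gives no such correlation and describes no baseline for pain, so this cannot carry an unqualified claim.

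Three further limits stand.

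- Missing a medium effect about two times in three describes a single day. Averaged over both visits (3 × 20), the miss rate is 34% to 61%.
- Large effects fare much better. They fall short of 0.8 on one day at 20 per group, pass it for 40 v 20 (0.82), and in the three-group test reach about 0.80 or more once visits are averaged.
- The article nowhere says that a null result will be read as no effect; that risk is a reviewer's inference. The remark on high power carries no figure and is conditional on normality.

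**Conclusion.** Wrong as written for treatment comparisons. Without baseline adjustment, a conventional medium effect has power 0.34 to 0.37 on one day at 20 per group, and 0.39 to 0.66 averaged over both visits in the three-group test. A large effect has 0.69 to 0.78 on one day and 0.80 to 0.98 averaged.

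The conclusion rests on conventional definitions of medium and large, a two-sided alpha of 0.05 and assumed correlations. It is firm for pain. For swelling and mouth opening it is conditional, because a strong baseline correlation could change it. The argument from 40 residual degrees of freedom does not show that 10 per group is enough. None of this shows that the trial must enrol more patients; it shows that the power statement should be replaced.

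**What to change.** 1. In Study design and composition of study sample, withdraw the sentence claiming power above 0.8 for medium and large effects, and the justification by 40 residual degrees of freedom. In Statistical analysis, delete the remark on high power.
2. Keep the arms given under Randomization (4 × 10 + 20 = 60, as in the Abstract). State that total throughout, since the article also gives totals of 50 and 40.
3. Report the differences detectable with 80% power, labelled as single-day, unadjusted and without multiplicity correction: about 0.78 SD for any laser v control (40 v 20), 0.90 SD for wavelength or site (20 v 20), and 1.10 SD for one laser arm v control (10 v 20).
4. Add that averaging visits, or adjusting for a well-correlated baseline where one exists, would reduce these by an amount that depends on correlations not yet stated. Say that medium effects are not powered for treatment comparisons in general.

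The cost is wording. The stated power becomes less favourable, no patients are added, and the change can be made while data collection continues.
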